### Sample size calculation

2.5

The sample size calculation is based on the two co-primary outcomes: NMD and GWE. The calculation is for a superiority trial, designed to achieve 80% statistical power at a two-sided significance level (α) of 0.05. No adjustment for multiplicity was applied to the co-primary outcomes (NMD and GWE) because they represent distinct physiological domains and address separate, independent research questions. NMD assesses the structural integrity and function of peripheral vascular smooth muscle (endothelium-independent pathway), whereas GWE serves as a specific metric for central myocardial energetics and metabolic efficiency. In the pathophysiology of T2DM, peripheral vascular remodeling and myocardial metabolic inflexibility are distinct complications that may progress asynchronously and respond to intervention via different mechanisms. Therefore, to capture the distinct effects of aerobic exercise on these independent physiological systems, each outcome was evaluated at a two-sided significance level of 0.05. All calculations were performed using PASS (Power Analysis and Sample Size) software. For GWE, as no direct data on the effects of AE exist, parameters are derived from a study on the effects of GLP-1 receptor agonists (GLP-1 RAs) in patients with T2DM. We hypothesized that the effect of AE would be 75% of that observed with GLP-1 RA treatment (20). This yields an estimated mean between-group difference (δ) of 2.7% with a projected standard deviation (σ) of 4.0%. This corresponds to a standardized effect size (Cohen’s d) of approximately 0.68, representing a “moderate-to-large” effect size. This estimation is considered conservative given that lifestyle and exercise interventions have previously demonstrated comparable or superior efficacy to medical interventions in key physiological domains. For example, the Diabetes Prevention Program showed that lifestyle intervention was more effective than metformin for the metabolic profile (21).

Based on these parameters, a minimum of 34 participants per group (n=68 total) is required to detect a significant difference. For NMD, the estimation is based on data from Ziegler et al., we estimated a mean intervention effect (δ) of 4.0% with a standard deviation (σ) of 5.6% (22). This calculation requires a minimum of 32 participants per group (n=64 total). To adequately power the study for both co-primary outcomes, we will use the larger of the two estimates. Therefore, the sample size is driven by the requirements for NMD. To account for a potential 10% dropout rate, we will recruit 37 participants per group, bringing the total sample size to 74.

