## Abstract

**Objective:**

Type 2 diabetes mellitus (T2DM) induces integrated cardiovascular and metabolic impairments. The comprehensive effect of aerobic exercise on these systemic alterations remains unclear. Therefore, we designed a randomized controlled trial to investigate its impact on integrated cardiovascular health — specifically assessed by nitroglycerin-mediated dilation (NMD) and myocardial global work efficiency (GWE) — and systemic energy metabolism in patients with T2DM.

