**Discussion:**

This study provides an integrated physiological perspective on how 12-week moderate-intensity aerobic exercise influences cardiovascular function and systemic metabolism in patients with T2DM. We hypothesize that 12 weeks of aerobic exercise will significantly improve NMD and GWE, concurrent with enhanced metabolic flexibility and reduced fatigue compared to the non-exercise control group.

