We hypothesize that a 12-week moderate-intensity aerobic exercise intervention will significantly enhance integrated cardiovascular function, specifically by improving GWE and NMD, while concurrently restoring systemic energy metabolism and metabolic flexibility in patients with T2DM. Furthermore, regarding the mechanisms of fatigue alleviation, we hypothesize that aerobic exercise will mitigate fatigue via a dual pathway: centrally, by modulating the balance of neurotransmitters (including serotonin, dopamine, and GABA), and peripherally, by reducing skeletal muscle injury biomarkers (CK and Myoglobin) and oxidative stress.

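### The multiplicity waiver treats NMD and GWE as separate questions, but the hypothesis joins them in one claim; if both are required, power is about 63–68%, not 80%

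*Protocol article*

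**What the plan says.** Section 2.5 (Sample size calculation) names NMD and GWE as co-primary. The calculation is "designed to achieve 80% statistical power at a two-sided significance level (α) of 0.05". On multiplicity it says: "No adjustment for multiplicity was applied to the co-primary outcomes (NMD and GWE) because they represent distinct physiological domains". It adds that the two outcomes "address separate, independent research questions" and that "each outcome was evaluated at a two-sided significance level of 0.05".

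The hypothesis is worded differently. The Introduction states that the intervention "will significantly enhance integrated cardiovascular function, specifically by improving GWE and NMD". The Discussion paragraph of the Abstract states that "12 weeks of aerobic exercise will significantly improve NMD and GWE". The Abstract's objective likewise presents NMD and GWE as the two measures of one construct, integrated cardiovascular health.

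On sample size, section 2.5 gives 34 per group for GWE and 32 for NMD, then says: "To adequately power the study for both co-primary outcomes, we will use the larger of the two estimates". It recruits 37 per group to allow for 10% dropout. Section 2.12 (Statistical analysis) repeats the 0.05 threshold and discusses multiple comparisons only for secondary outcomes.

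**The concern.** Waiving adjustment is coherent when each outcome carries its own conclusion. The objective and hypothesis do not set up two conclusions. They set up one, about integrated cardiovascular function, with NMD and GWE as its two components. The reason given for the waiver therefore does not fit the claim the trial intends to make.

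This matters most for a split result. If NMD is significant and GWE is not, section 2.5 would treat NMD as a positive answer to its own question, while the Introduction's hypothesis, read as worded, would not be met. Nothing in the text stops the split result from being presented as support for the integrated hypothesis. It also matters for what the trial can deliver: if both outcomes must succeed, a sample size chosen one outcome at a time gives less than 80% chance of success.

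**Working it through.** **Inputs (section 2.5).** GWE: difference 2.7, SD 4.0. NMD: difference 4.0, SD 5.6. Two-sided alpha 0.05, power 80%, 37 per group recruited, 10% dropout. Completers: 37 × 0.90 = 33.3, taken as 33 per group. The correlation between the two test statistics is not given; I assume 0 to 0.5 and show 0.8 as an extreme.

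**The plan's own sample sizes.** With d = difference / SD and n per group = 2(1.960 + 0.842)² / d²:

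- GWE: d = 2.7 / 4.0 = 0.675 gives 34.5, so 35 (36 by the exact t-test). The rounded d of 0.68 gives 33.9, hence the stated 34.
- NMD: d = 4.0 / 5.6 = 0.714 gives 30.8, so 31 (32 by the exact t-test, as stated).

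The stated figures reproduce to within two patients per group.

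**Power for each outcome** (two-sample t-test, noncentral t):

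| Completers per group | GWE | NMD |
|---|---|---|
| 33 | 77.1% | 81.5% |
| 37 (no dropout) | 81.7% | 85.8% |

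**Power for both outcomes.** At correlation 0 this is the product: 0.7705 × 0.8153 = 0.628 at 33 per group, and 0.8171 × 0.8579 = 0.701 at 37. At other correlations it is a bivariate normal probability with these marginal powers:

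| Completers per group | r = 0 | r = 0.3 | r = 0.5 | r = 0.8 |
|---|---|---|---|---|
| 33 | 62.8% | 65.5% | 67.6% | 71.8% |
| 37 | 70.1% | 72.2% | 73.9% | 77.4% |

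No cell reaches 80%. Joint power of 80% would need 44 completers per group at r = 0 and 42 at r = 0.5.

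**False-positive rates with both nulls true, each outcome tested at 0.05:**

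- If one significant outcome were allowed to carry the claim: 1 − 0.95² = 9.75% at r = 0, 9.5% at r = 0.3, 9.1% at r = 0.5.
- If both are required: 0.05² = 0.25% at r = 0, 0.9% at r = 0.5. If only one null is true, the rate cannot exceed 5%.

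**Hochberg rule for the fix** (claim both if both p < 0.05; otherwise claim the outcome with the smaller p if it is below 0.025):

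- Family-wise error at r = 0: 0.05² + 2 × 0.025 × 0.95 = 0.050. At r = 0.5 it is 0.048.
- Power at 33 per group, r = 0. Power at alpha 0.025 is 67.2% (GWE) and 72.7% (NMD). GWE: 0.628 + 0.672 × (1 − 0.815) = 75.2%. NMD: 0.628 + 0.727 × (1 − 0.771) = 79.5%. The losses are 1.8 and 2.0 points. At r = 0.5 they are 2.4 and 3.0 points.

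**The case against.** Multiplicity was considered: section 2.5 states a decision, a physiological reason and a threshold. If each outcome is reported strictly as its own conclusion, testing each at 0.05 is defensible, and neither the 10% error nor the joint power is the relevant figure. That stands, but it needs two separate conclusions, and the Abstract and Introduction draw one.

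A reader might infer that the plan doubles its false-positive rate to about 10%. The documents do not support this. No section says that either outcome alone is enough. Both statements of the hypothesis join the outcomes with *and*, and for that claim testing each at 0.05 already holds the error at or below 5%. The 9.1–9.8% describes a way of reporting that the text leaves open, not one that it adopts.

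Powering for both can also be read as powering for each, and taking the larger of two sample sizes is the usual way to do that. This is a fair reading; the wording does not settle it. Finally, part of the shortfall in joint power comes from GWE itself falling to 77% after dropout, which is a sample-size matter. That too is right, but with no dropout, when each outcome exceeds 80%, joint power is still only 70–77%.

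**Conclusion.** The inconsistency is real and should be fixed. Section 2.5 justifies its testing rule by separate questions, while the objective and hypothesis make one conjunctive claim. Read as worded, that claim needs no alpha adjustment, but its power is about 63–68% at 33 completers per arm with correlation 0 to 0.5, and 70–77% with no dropout and correlation 0 to 0.8. The correlations are assumed, and the effects and SDs are the plan's own. That joint power falls short of 80% does not depend on which of these values is chosen.

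Inflation to 9.1–9.8% is conditional: it needs both nulls true and a single win reported as the integrated result. It is a reason to close the gap in wording, not an error rate of the plan as written. The remedy leaves the design, data collection and models unchanged, so this is a should-fix rather than a must-fix point. It does change what the trial may conclude, so it should be settled before any comparison of the groups.

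**What to change.** 1. In section 2.5, state that the integrated-cardiovascular claim requires both NMD and GWE to be significant at two-sided 0.05. Replace the separate-questions rationale with this rule, which needs no adjustment.
2. Replace the sentence on powering for both outcomes with the figures: about 77% for GWE and 82% for NMD after 10% dropout, and joint power of about 63–68% for an assumed correlation of 0 to 0.5.
3. State that if only one outcome is significant, it is reported as a single-outcome result and never as support for the integrated hypothesis. Use Hochberg for such claims. Holm would conflict with item 1: p-values of 0.03 and 0.04 would support the integrated claim, yet Holm would allow neither single claim. Under Hochberg the two rules agree.

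Keeping the waiver and dropping the integrated conclusion in favour of two separate claims would also be consistent, but it gives up the question the trial was set up to answer.

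The cost is wording, about 2–3 points of power per outcome for single-outcome claims, and a stated joint power that looks less favourable than 80%. No additional patients or measurements are needed.

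### The sample-size section names NMD as the outcome that sets the size when GWE does, and 37 per group at 10% dropout falls one short of its own minimum, leaving GWE power at about 77–78% rather than 80% (minor)

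*Protocol article*

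**What the plan says.** Section 2.5 (Sample size calculation) sizes the trial on two co-primary outcomes. The calculation is "designed to achieve 80% statistical power at a two-sided significance level (α) of 0.05", and without a multiplicity adjustment "each outcome was evaluated at a two-sided significance level of 0.05".

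- **GWE.** "This yields an estimated mean between-group difference (δ) of 2.7% with a projected standard deviation (σ) of 4.0" per cent. The standardised effect is given as a Cohen's d "of approximately 0.68, representing a" moderate-to-large effect. On these parameters, "a minimum of 34 participants per group (n=68 total) is required to detect a significant difference".
- **NMD.** "we estimated a mean intervention effect (δ) of 4.0% with a standard deviation (σ) of 5.6" per cent, for which the section requires 32 per group (64 in total).
- **Choice of size.** The section says it takes the larger of the two, and then: "Therefore, the sample size is driven by the requirements for NMD".
- **Dropout.** "To account for a potential 10% dropout rate, we will recruit 37 participants per group, bringing the total sample size to 74".

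**The concern.** The rule and the conclusion drawn from it disagree within a few lines: the larger of 34 and 32 is the GWE figure, yet NMD is named. The recruited number also looks one short per group, since taking 10% off 37 does not leave 34.

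What is at stake is the accuracy of the power statement. Each co-primary outcome is tested on its own at 0.05 as a separate question, so adequate power for NMD does not make up for a shortfall on GWE. The shortfall falls on the outcome that actually determines the size. A reader interpreting a null GWE result would be relying on an 80% that the printed inputs do not quite support.

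**Working it through.** **Inputs (all from section 2.5; the 1:1 ratio is in section 2.1).** Two-sided α = 0.05; power 80%; equal groups. GWE: δ = 2.7, σ = 4.0, so d = 2.7/4.0 = 0.675 (printed as about 0.68). NMD: δ = 4.0, σ = 5.6, so d = 4.0/5.6 = 0.714. Dropout 10%; 37 recruited per group.

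**Formulas.** Normal approximation: n per group = 2(1.960 + 0.842)²/d² = 15.70/d². t-test: the smallest n at which the non-central t distribution, with 2n − 2 degrees of freedom and non-centrality d√(n/2), gives at least 80% power.

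**Step 1. Reproduce the plan's figures.** With d rounded to two decimals and the normal approximation:

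- GWE: 15.70/0.68² = 33.95, so 34.
- NMD: 15.70/0.71² = 31.14, so 32.

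Both stated minima are recovered by this one method.

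**Step 2. Use the printed δ and σ without rounding d.**

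| Outcome | d | Normal approximation | t-test | Stated |
|---|---|---|---|---|
| GWE | 0.675 | 34.45, so 35 | 36 | 34 |
| NMD | 0.714 | 30.77, so 31 | 32 | 32 |

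GWE is the larger requirement under either method.

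**Step 3. Which outcome lies behind 37?** For NMD, 32/0.9 = 35.6, so 36. For GWE, 34/0.9 = 37.8, so 38. The recruited 37 exceeds the inflated NMD requirement and falls just under the inflated GWE requirement, so NMD does not explain it.

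**Step 4. Dropout.** 37 × 0.9 = 33.3 per group (74 × 0.9 = 66.6 in total, against 68 required). Recruiting 37 keeps 34 only if loss is at most 1 − 34/37 = 8.1%. Recruiting 38 would leave 38 × 0.9 = 34.2.

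**Step 5. Power under the printed inputs, by evaluable number per arm.**

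| Evaluable per arm | GWE, normal | GWE, t-test | NMD, normal | NMD, t-test |
|---|---|---|---|---|
| 33 | 78.3% | 77.1% | 82.7% | 81.5% |
| 34 | 79.5% | 78.3% | 83.8% | 82.7% |
| 37 (no loss) | 82.7% | 81.7% | 86.7% | 85.8% |

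Rounding 33.3 down to 33 matters little: at 33.3 per arm, GWE power is 78.6% (normal) or 77.4% (t-test). If dropout is instead allowed to vary at random around 10% in each arm of 37, average t-test power is 77.3% for GWE and 81.8% for NMD.

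**The case against.** The strongest reply is that the difference is trivial and the power figures are conditional. The shortfall against the plan's own minimum is one participant per group. The GWE effect is itself a hypothesised 75% of a drug effect, an uncertainty far larger than two or three points of power. Section 2.12 plans a linear mixed model on all randomised participants with medication covariates, not a t-test, and section 2.5 does not say whether its SDs describe change or 12-week values. Power under the planned model could be higher or lower. Section 2.1 also intends to follow everyone regardless of adherence or completion; if all 37 per group gave 12-week data, GWE power would be 81.7% even on the t-test.

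Most of this stands, and it limits the point to a minor one. It does not rescue the text. The driver sentence is wrong under any analysis model. The 10% loss is the plan's own allowance. No baseline-to-follow-up correlation is given from which a higher power could be claimed.

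Three stronger readings are tempting, and the document does not support them:

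- **That the two minima were calculated by different methods.** Comparing the unrounded NMD effect with the rounded GWE effect suggests this, but step 1 shows that one method with both effects rounded to two decimals gives both figures.
- **That dropout was computed as 34 × 1.1 = 37.4 and rounded down.** The section shows no dropout formula, and 34/0.9 = 37.8 cut to 37 fits equally well. Only the shortfall is established, not how it arose.
- **That 34 can arise in no other way than by rounding d to 0.68.** δ and σ are printed to one decimal. Values such as 2.74 and 3.96 (d = 0.692) would print the same and give 34 on a t-test. What can be said is that the figures as printed need 35 or 36.

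**Conclusion.** Wrong as written, and minor. Two statements follow from the section's own numbers without any modelling: GWE (34), not NMD (32), determines the size; and 37 per group at 10% dropout leaves about 33, one below the stated minimum of 34.

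The power consequence is small. With 33 evaluable per arm, GWE has about 77% (t-test) to 78% (normal approximation) rather than 80%, a gap of roughly 1.7 to 2.9 percentage points. NMD stays above its target at about 82–83%. These figures assume that the printed δ and σ hold, that the SD applies to the contrast actually analysed, that loss is 10% in each arm, and that dropouts contribute no 12-week data. A reader might infer a seriously underpowered trial; the numbers do not show that.

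**What to change.** Correct section 2.5, leaving enrolment at 74:

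1. Name GWE as the outcome that determines the sample size.
2. Show the dropout step as n/(1 − 0.10), so that a reader can see that 34 evaluable corresponds to 37.8 recruited, which rounds up to 38, and that 37 is one below this.
3. Give the GWE requirement from the unrounded d of 0.675 (35 by normal approximation, 36 by t-test), or say that 34 uses the rounded 0.68, and name the method.
4. Restate the power for 74 randomised at 10% loss as about 77–78% for GWE and 82–83% for NMD, with the assumptions that the stated SD applies to the analysed contrast and that dropouts give no 12-week data.

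The cost is a change of wording and a slightly less favourable GWE power statement. No analysis changes. Recruitment is described as ongoing, so the correction can be made before results are known. If the sponsor preferred to keep a claim of 80% for GWE under the printed inputs, the recruited number would have to be 35/0.9 = 38.9, so 39 per group (normal approximation), or 36/0.9 = 40 per group (t-test). The point does not require that.

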### Research design

2.1

This study is a single-assessor-blind, parallel-group, two-arm randomized controlled trial. Participants will be randomly assigned in a 1:1 ratio to either a 12-week aerobic exercise group (AE group) or a non-exercise control group (Con group). Clinical assessments will be performed at baseline (pre-intervention) and at the 12-week follow-up. A detailed schedule of enrollment, interventions, and assessments is presented in **Table 1**. Considering the minimum clinically effective dose of exercise, adherence to the intervention will be defined as the completion of at least 80% of the prescribed exercise sessions. Participants who do not meet this threshold will be categorized as non-adherent. To minimize attrition bias, all participants, regardless of their adherence or completion of the intervention, will be followed up and included in the primary analysis according to the intention-to-treat (ITT) principle. Written informed consent will be obtained from all participants before enrollment. The reporting of this trial will adhere to the Consolidated Standards of Reporting Trials (CONSORT) statement.

**Table 1 T1:** Participant timeline: schedule of enrollment, interventions, and assessments.

Trial period	Enrollment		Post-randomization			Close-out
Timepoint	Screening *(Day-12 to 0)*	Baseline *(Day0)*	Intervention Period *(Weeks 1-6)*	Intervention Period *(Day42)*	Intervention Period *(Weeks 6-12)*	*Week 12 (± 3 days)*
Enrollment:						
Eligibility screen	X					
Informed consent	X					
Medical history	X					
Randomization		X				
Intervention:						
Aerobic Exercise Group		X				X
Control Group		X				X
Assessments:						
Primary outcomes						
nitroglycerin-mediated dilation		X				X
myocardial global work efficiency		X				X
Secondary outcomes						
Energy Metabolism		X				X
Peak Heart Rate (HR_peak_)		X		X		X
Traditional Cardiovascular Risk Factors		X				X
Cardiovascular & Cardiopulmonary Function		X				X
Self-reported fatigue assessment		X				X
24-hour physical activity monitoring		X				X
Circulating biomarkers		X				X
Safety monitoring						
Adverse Events		X				X

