### Statistical analysis

2.12

All statistical analyses will be performed using R software (version 4.3.1 or later; R Foundation for Statistical Computing, Vienna, Austria). For the description of baseline data, normally distributed continuous variables will be presented as 
mean±standard deviation (SD), while non-normally distributed variables will be reported as median [interquartile range (IQR)]; categorical variables will be expressed as frequencies and percentages (n, %). For the comparison of baseline data between groups, independent samples t-tests will be used for normally distributed continuous variables, the Mann-Whitney U test will be used for non-normally distributed data, and the chi-square (χ²) test or Fisher’s exact test will be used for categorical data.

Efficacy analyses will be conducted according to the intention-to-treat (ITT) principle and will include all randomized participants. Continuous outcomes, including NMD and GWE, will be analyzed using linear mixed-effects models (LMMs). To rigorously control for potential confounding, background medication use will be prespecified and included as fixed-effect covariates in the models. Medications will be categorized by therapeutic class, with binary indicators (yes/no) created for: (1) glucose-lowering agents (with separate indicators for GLP-1 receptor agonists and SGLT2 inhibitors), (2) antihypertensive medications, and (3) statins. Each LMM will incorporate group, time, and the 
group×time  interaction as fixed effects, with a random intercept for each participant to account for repeated measurements.

Sensitivity analyses will be performed using multiple imputation to assess the robustness of the findings under different assumptions regarding missing data. In addition, a per-protocol (PP) analysis will be conducted as a secondary sensitivity analysis, including only participants with an attendance rate of at least 80%. Secondary outcomes will be considered exploratory and hypothesis-generating; therefore, no adjustment for multiple comparisons will be applied. A two–tailed *P*–value < 0.05 will be considered statistically significant.

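### The 10% dropout allowance covers only lost observations, yet non-completers stay in the primary ITT analysis; GWE power at 37 per group is about 73–78%, not 80%

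*Protocol article*

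**What the plan says.** Section 2.5 (Sample size calculation) describes a trial "designed to achieve 80% statistical power at a two-sided significance level (α) of 0.05". For GWE it uses an "estimated mean between-group difference (δ) of 2.7% with a projected standard deviation (σ) of 4.0" percentage points, described as a "standardized effect size (Cohen’s d) of approximately 0.68", and arrives at 34 per group. For NMD it uses a difference of 4.0 with SD 5.6 and arrives at 32 per group. It then adds the allowance: "To account for a potential 10% dropout rate, we will recruit 37 participants per group, bringing the total sample size to 74". Neither difference is reduced for participants who stop exercising.

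Section 2.1 (Research design) says that "all participants, regardless of their adherence or completion of the intervention, will be followed up and included in the primary analysis". It also sets the adherence cut-off: "Considering the minimum clinically effective dose of exercise, adherence to the intervention will be defined as the completion of at least 80" per cent of prescribed sessions.

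Section 2.12 (Statistical analysis) repeats the analysis set: "Efficacy analyses will be conducted according to the intention-to-treat (ITT) principle and will include all randomized participants". It plans multiple imputation as a sensitivity analysis, so some missing outcomes are expected, and a per-protocol analysis at 80% attendance or more, so some participants are expected to fall below that level.

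**The concern.** Enlarging the sample for dropout is the right correction when dropouts contribute no outcome: the number analysed shrinks and the effect among those left is unchanged. The plan describes a different handling of people who stop exercising. They are to be measured and counted in the exercise mean. Their effect on power then works through the size of the difference, and a larger head-count does not stand in for a smaller difference in any fixed way.

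The plan's wording makes some dilution plausible. It justifies the 80% attendance cut-off by the smallest dose of exercise expected to work clinically, so people below it receive less than that dose by the plan's own description, yet they belong to the primary comparison.

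At stake is how a null GWE result would be read. If the trial is described as having 80% power and the primary analysis has less, a non-significant result will be taken as stronger evidence against an effect than it is.

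**Working it through.** **Inputs, all from section 2.5 unless noted.** Two-sided α = 0.05, target power 80%, 1:1 allocation. GWE: δ = 2.7, σ = 4.0. NMD: δ = 4.0, σ = 5.6. Dropout 10%, 37 recruited per group. Non-completers are kept in the primary analysis (sections 2.1 and 2.12). Power is that of a two-sample t-test on the change from baseline, with the printed σ taken as the SD of that change. The planned mixed model's medication covariates are ignored, because the article gives no figure for their effect on precision.

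**1. Reproducing the plan's numbers.**
- Normal formula: n = 2(1.960 + 0.842)²/d² = 15.70/d².
- GWE with the rounded d = 0.68: 15.70/0.4624 = 33.95, so 34 as printed. With the unrounded d = 2.7/4.0 = 0.675: 15.70/0.4556 = 34.45, so 35. The t-based calculation gives 36.
- NMD, d = 4.0/5.6 = 0.714: 31 by the normal formula and 32 by the t-based calculation, against 32 printed.
- Dropout: 34/0.9 = 37.8 and 34 × 1.1 = 37.4. Both round up to 38, against 37 printed. Conversely 37 × 0.9 = 33.3, which is below 34.

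**2. Power under each reading of the 10%.** Non-centrality = δ/(σ√(2/n)), with 2n − 2 degrees of freedom.

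| Reading | n per group | GWE δ | GWE power | NMD δ | NMD power |
|---|---|---|---|---|---|
| No loss, no dilution | 37 | 2.70 | 81.7% | 4.0 | 85.8% |
| 10% of each group has no week-12 outcome | 33 | 2.70 | 77.1% | 4.0 | 81.5% |
| 10% of exercisers stop, all measured, half the benefit kept | 37 | 0.95 × 2.7 = 2.565 | 77.7% | 0.95 × 4.0 = 3.8 | 82.1% |
| 10% of exercisers stop, all measured, no benefit | 37 | 0.90 × 2.7 = 2.43 | 73.2% | 0.90 × 4.0 = 3.6 | 77.9% |

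In the last row the exercise arm is a mixture of responders and non-responders. Its variance becomes 16 + 0.1 × 0.9 × 2.7² = 16.66, the SD averaged over both arms is about 4.04, and GWE power is 72.3%.

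**3. What would rescue 80% for GWE.** With all 37 per group measured, 80% power needs δ of about 2.64, which is 0.978 of 2.7. If stoppers keep a fraction r of the effect, 0.9 + 0.1r = 0.978, so r is about 0.78.

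**4. Separating the causes.** With the 10% simply lost, GWE power is already 77.1%. That shortfall comes from the rounded d and normal formula behind 34 and from rounding down to 37. Replacing loss by no-benefit dilution moves 77.1% to 73.2%, a further 3.9 points.

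**The case against.** The strongest reply is that the sections need not conflict. Dropout is not defined, and its usual meaning in a sample size section is a missing final outcome. The plan foresees missing data. One can intend to follow everyone and still allow for those who cannot be reached; enlarging the sample is then the right kind of correction. This stands, and it is why loss is one of the readings tabulated. It does not restore 80% for GWE, because that reading gives about 77%.

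A reader might infer that the plan's power is simply 73%. The documents do not support that. The figure needs the 10% to be exercisers who stop, all of them to be measured at week 12, none of them to benefit, and δ to be an effect in adherent participants. None of these is stated. The adherence cut-off refers to a minimum effective dose, but it does not say that attendance just below 80% has no effect on GWE.

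Nor does the article say that 2.7 or 4.0 are full-adherence effects. The GWE value is an assumed 75% of a drug effect, called conservative, and the NMD value is described as a mean intervention effect. Whether either source already includes non-adherence cannot be judged from the article. It would be wrong to ask the authors to declare these values adherence effects; they should say which they are.

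It is also fair that the whole gap from 80% to 73% cannot be put down to dilution, as step 4 shows.

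**Conclusion.** The point holds in a conditional form. The allowance replaces lost observations only, the primary analysis keeps non-completers, and the assumed differences carry no stated reduction for them. For GWE the claimed 80% is missed on each reading of the 10% tabulated: about 77% with loss, 78% with half the benefit retained, 73% with none. It is reached only if everyone is measured and stoppers keep roughly 78% or more of the effect, or if 2.7 is already an ITT difference and all 37 per group are measured. For NMD the target is met under loss and under half benefit (about 82% each) and missed only under no benefit (about 78%).

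The shortfall is modest, between about 2 and 7 points for GWE, of which dilution in place of loss accounts for at most about 4. The 10% is the plan's figure; the benefit kept by stoppers is an assumption, and the range shows its effect. The results rest on the printed SDs and on a t-test standing in for the mixed model.

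**What to change.** In section 2.5:
- Say whether the 10% means stopping exercise or having no week-12 outcome.
- Say whether the differences of 2.7 and 4.0 are meant as ITT effects or as effects in adherent participants.
- Replace the 80% claim for GWE with the power of the planned ITT analysis at 37 per group. If 2.7 is an adherent-participant effect, suitable wording is: about 73% to 78% at 10% non-completion, the lower figure if exercisers who stop are measured with no benefit, the upper if they keep half of it, and about 77% if the 10% are not measured. Give NMD on the same basis, about 78% to 82%.
- State that a non-significant GWE result will be interpreted from its confidence interval.

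Keep the total of 74 and the ITT primary analysis. The change costs wording only, with no extra participants or procedures. Its one drawback is that the stated power becomes slightly less favourable.
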